#### Rationale: There is a lack of evidence about the level of risk different handwashing methods pose for the disruption of the natural skin barrier on hands and development of irritant contact dermatitis. In both traditional healthcare settings and in disease outbreak settings there is a strong need for methods that both provide adequate hand disinfection and protect healthcare workers from the added risk that ICD may pose by disrupting skin’s natural protection. Healthcare workers and the dermatologists who treat occupationally acquired ICD are seeking clearer recommendations for regular handwashing and alternative suggestions for individuals displaying particular sensitivity to commonly used methods, and the international humanitarian community is asking for consistent evidence-based guidance on handwashing in the particularly risky situations where they face highly dangerous infectious diseases such as EVD.

It is difficult to distinguish the causes of dermatitis in these populations, since healthcare workers and all those who wash hands regularly are commonly exposed to a range of substances acting as irritants that may cause dermatitis1. Therefore there is a need to study the impact of these handwashing methods while controlling for other substances that may cause a skin reaction. The results of this study will provide evidence-based recommendations aligning contradictory guidance to healthcare workers in settings across the globe, and are particularly relevant to international organizations concerned with the most recent EVD outbreak. The outbreak in West Africa is the largest to date, establishing the potential for large and devastating outbreaks with reproductive rates >115. Clear handwashing protocols are an essential practical recommendation to prevent future outbreaks attaining the size and duration of the most recent outbreak devastating West Africa.

1. **Research Plan**

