### Experimental design:

### This study consists of an individually randomized controlled trial with six arms to assess the impact of six different methods of frequent handwashing (soap and water, hand sanitizer, 0.05% chlorine solution made with NaDCC, 0.05% chlorine solution made with HTH, 0.05% stabilized chlorine solution made with NaOCl, 0.05% unstabilized chlorine solution made with NaOCl) on development of dermatitis.

*Recruitment and Enrollment*: Subjects will be recruited using flyers posted around the Medford/Somerville area and newspaper advertisements taken out in the Tufts Daily, the Somerville Journal and the Medford Journal (Appendix A). These advertisements will describe the purpose and requirements of the study and provide contact information for the study team. The flyer will also be distributed as an image to public listservs and social media groups such as the Medford Moms email list and Tufts campus email lists. Individuals who feel that they meet the study’s criteria may attend one of several 1 hour meetings during which researchers will explain the study in detail (Frequently Asked Questions in Appendix B). Potential volunteers will be given the opportunity to ask questions about the study in a group setting. After the meeting subjects will meet with researchers individually to ask further questions they may be uncomfortable asking in a public setting and study staff will collect written informed consent (Appendix C) in a private setting. Subjects who consent to the study will then be asked to schedule a time to complete the baseline survey and data collection. Potential volunteers who do not wish to attend a group meeting or are unable to attend at the posted time may schedule a meeting with researchers to learn about the study individually and provide informed consent if they choose to participate.

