### Sample size and statistical analysis(es) :

### We plan to enroll 108 total subjects in the study, with 18 randomized to each arm. We will target this number with the understanding that minor attrition may occur, and estimate that we need 15 subjects per arm to complete the study to achieve our goals.

**Randomization Methods**: Randomization will be done after patch-testing results are read, to ensure that no subjects meeting exclusion criteria are involved in the study intervention. A researcher who does not interact directly with subjects will perform randomization. Subjects will be numbered (1-108). 18 subjects will be assigned to each group. A random number generated will be used to generate 18 numbers between 1 and 108. These subjects will be assigned to the first intervention group. Random number generation will be repeated in this way five times, with subjects corresponding to the number assigned to the treatment group for the round. The 18 remaining subjects will be assigned to the last treatment group.

**Blinding**: Researchers assessing HECSI scores for the hand exam and applying and interpreting results of the patch testing will be blinded to subject treatment group. Daily surveys will not record treatment arm and subjects will be instructed not to identify their group to examiners.

It is not possible to blind subjects to treatment, because the difference between soap and water, hand sanitizer, and chlorine solutions are obvious and cannot be obscured. However subjects assigned to one of the chlorine solution treatment groups will not be told which solution they have been assigned.

**Sample Size Calculations:** Because there are no previous handwashing studies using chlorine, soap, or hand sanitizer for handwashing that can provide information on the number of subjects likely to develop dermatitis we are unable to calculate a meaningful sample size for statistical significance. We feel that this small sample size is appropriate for a first study. For example if 20-100% of participants in a given arm develop dermatitis that will suggest that the method is problematic and should not be recommended, but if 0% of participants develop dermatitis this will be good evidence that the method has potential and should be studied further. This study is intended to be a first investigation that can provide information that could be used in the future for sample size calculations for a larger trial if any of the handwashing materials show potential.

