Contact information including phone number and email address will be collected for each patient, and patients will be notified of any changes in the study in writing either through email or in person. These written records of changes will be archived and a description of changes included in any write up of study methods.

1. **Payment, including a prorated plan for payment**: Subjects will receive a total of $600 after successful completion of all study activities. Subjects will receive $100 for each round of patch testing is completed, and $100 for each week of the intervention completed. Although this study presents minimal risk to subjects, a high level of compensation is called for due to the study’s labor-intensive nature including consistent attention to details and the high level of compliance to intervention activities and attendance at assessments over the course of 7 weeks and the inconvenience of patch testing procedures. The fees will be paid in three stages: $100 after the baseline assessment, $200 at the midpoint of the intervention, and $300 after the endline assessment.
2. **Payment for a research-related injury**: [name] will examine any subjects showing signs of dermatitis. Over the counter treatment will be provided by the research team if necessary, but subjects will be covered by personal medical insurance for consultations at [name] clinic. If subjects do not have sufficient insurance the study will cover the costs of this consultation. Subjects will be reimbursed up to $100 for transportation to a consultation at [name] office. Subjects will not be financially compensated for any research-related injuries.
3. **Outcome**: We expect low levels of our primary outcome of dermatitis (as measured by visual dermatitis scale assessed by study staff) and secondary outcome of discomfort (as measured by self-perception of hand feel) and any level of dermatitis, including 0%, will provide valuable data. However a high level of compliance is necessary for the success of the study and will be measured by self-report and observation of materials. We define high compliance as >95% completion of study intervention activities, as measured by survey completion, pickup of materials, and self reported handwashing 10x per day.

1. **Tissue banking considerations**: None

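### Fifteen completers per arm cannot support the reading that dermatitis in 20% or more of an arm means the method should not be recommended

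*Protocol*

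**What the plan says.** The study is an "individually randomized controlled trial with six arms". On size, the section *Sample size and statistical analysis(es)* states "We plan to enroll 108 total subjects in the study, with 18 randomized to each arm", and the authors "estimate that we need 15 subjects per arm to complete the study to achieve our goals".

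Under *Sample Size Calculations* they write that "we are unable to calculate a meaningful sample size for statistical significance", and that a small sample suits a first study. They then illustrate how results would be read. At the upper end, "if 20-100% of participants in a given arm develop dermatitis that will suggest that the method is problematic and should not be recommended". At the lower end, "if 0% of participants develop dermatitis this will be good evidence that the method has potential and should be studied further". Observed rates above 0% and below 20% are not mentioned, and no interval or error rate is attached to either reading.

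Three other places bear on this:

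- *Data Analysis* calls the analysis descriptive and plans to compare the proportion with dermatitis between the groups.
- *Outcome*, under Subject Participation, says "We expect low levels of our primary outcome of dermatitis" and gives no number.
- *Rationale* says "The results of this study will provide evidence-based recommendations aligning contradictory guidance to healthcare workers".

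**The concern.** The upper reading attaches a conclusion about practice to a raw percentage in one arm. With 15 completers each subject is worth 6.7 percentage points (1/15), so an arm with no cases and an arm labelled unfit to recommend are three people apart. Six arms are read this way, which gives chance six opportunities to produce the label.

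The reading is also absolute. The aim and hypothesis ask whether dermatitis differs by substance, yet the 20% cut applies to an arm on its own. A chlorine arm at 20% would get the adverse label whether soap and water gave 0% or 40%.

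At stake is a method being set aside without evidence that it is worse than the others, in a trial whose Rationale promises guidance for health workers and outbreak response.

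**Working it through.** **Inputs.** Six arms, 18 randomised and 15 completers per arm, and the cuts at 0% and 20%, all from the protocol. The protocol gives no expected rate, so a range of true rates *p* is assumed. Subjects are treated as independent, each with or without dermatitis.

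**1. The plan's own figures.** 6 × 18 = 108 agrees. Going from 18 to 15 allows a loss of 3/18 = 16.7%, but no attrition rate is stated. The 15 follows from no stated input, so it cannot be reproduced.

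**2. The cut as a count.** 0.20 × 15 = 3, so 3/15 triggers the adverse reading. 0.20 × 18 = 3.6, so with full retention it takes 4/18 (22.2%).

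**3. Precision (Clopper–Pearson, 95%).**

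- 0/15: upper limit 1 − 0.025^(1/15) = 21.8%; one-sided, 1 − 0.05^(1/15) = 18.1%.
- 3/15: 4.3% to 48.1%.
- 0/18: upper limit 18.5%. 4/18: 6.4% to 47.6%.

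At n = 15 the intervals for the two classes overlap from 4.3% to 21.8%.

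**4. Can 3/15 be told from 0/15?** The probability that all three events fall in one named arm is C(15,3)/C(30,3) = 455/4,060 = 0.112; two-sided, p = 0.224. The difference is 20 points with a Newcombe 95% interval of −4.2 to +45.2. Against 0/15, the first count with p < 0.05 is 5/15 (p = 0.042). For 0/18 v 4/18, p = 0.10.

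**5. Six methods with the same true rate.** Let P0 = (1 − p)^n, and let Ph be the binomial probability of at least 3/15 (or 4/18).

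- At least one arm with the adverse label: 1 − (1 − Ph)^6.
- At least one arm in each class: 1 − (1 − P0)^6 − (1 − Ph)^6 + (1 − P0 − Ph)^6.

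Worked at p = 10%, n = 15: P0 = 0.9^15 = 0.206 and Ph = 0.184. The first is 1 − 0.816^6 = 0.705. The second is 1 − 0.794^6 − 0.816^6 + 0.610^6 = 0.506.

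| True rate, all arms | One arm ≥ 3/15 | Any adverse label, n = 15 | Both classes, n = 15 | Any adverse label, n = 18 | Both classes, n = 18 |
|---|---|---|---|---|---|
| 2% | 0.3% | 2% | 2% | 0.2% | 0.2% |
| 5% | 3.6% | 20% | 19% | 6% | 6% |
| 8% | 11% | 51% | 43% | 27% | 19% |
| 10% | 18% | 70% | 51% | 46% | 27% |
| 15% | 40% | 95% | 39% | 86% | 23% |

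The chance that both classes appear peaks at 51% near a true 11% with n = 15, and at 28% with n = 18. For one given pair of identical arms (2 × P0 × Ph) it is at most about 8%.

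**6. The 0% reading.** A true 20% rate gives 0/15 with probability 0.8^15 = 3.5%. A clean arm is therefore some evidence against a rate that high.

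**The case against.** The passage is introduced as an example, uses the language of suggestion, and sits in a study that calls itself preliminary and descriptive. On that view it is not a decision rule, and the silence on 1/15 and 2/15 is a defect only if the two readings were meant to be exhaustive, which the protocol does not say. This stands as a limit on severity. It does not rescue the clause, because a statement about what should be recommended is a practice conclusion whatever introduces it, and the Rationale makes the same promise without the caveat. *Risk/benefit assessment* is milder, referring to recommendations from this and later studies.

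A reader might go further and infer three things the documents do not support:

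- **That the whole two-class reading fails.** The 0% branch claims only potential and a case for further study. 0/15 supports that (step 6), and the one-sided upper limit of 18.1% lies below 20%. Only the two-sided limit at n = 15 passes it.
- **That identical methods would often be sorted into opposite classes.** This depends on a rate the protocol does not give. At true rates of 2% to 5%, which fit its expectation of low levels, the chance is 2% to 19% with n = 15. The 51% is close to the worst case. Likewise, 1 or 2 events in 15 are together likelier than none only above a true rate of about 5%.
- **That the trial would be read as six single-arm studies.** *Data Analysis* does plan a comparison between groups. What lacks a comparator is the 20% cut, and in the 40% soap example the soap arm would be labelled too.

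**Conclusion.** The point holds for the upper reading. An observed 20% in an arm of 15 is compatible with true rates from about 4% to 48%, is not separable from 0/15, and is judged without the concurrent control. If the six methods were identical, at least one would get the adverse label with a probability that runs from about 2% at a true 2% to 70% at a true 10% with 15 completers, or 0.2% to 46% with all 18.

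These probabilities rest on a common true rate, independent subjects and equal arm sizes of 15 or 18. They are shown as a range because the protocol supplies no rate. The interval and the Fisher result need no assumed rate.

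**What to change.** - In *Sample Size Calculations*, delete the clause on not recommending a method and limit the conclusion to which methods merit further study. The 0% sentence can stay.
- State that each arm's proportion will be read with its exact 95% interval, and its difference from soap and water with a 95% interval.
- State that 0/15 rules out only rates above about 22% (two-sided; 18% one-sided), and that results between 0% and 20% are undetermined.
- In *Rationale*, bring the promise of recommendations into line with the preliminary, descriptive status given in *Data Analysis* and *Sample Size Calculations*.

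An overall test across the six arms is optional in a descriptive study and is not part of this correction. The cost is protocol wording, a few lines of analysis and a less favourable stated conclusion. Design, data collection and subject numbers do not change.

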### Subject Characteristics

- 1. *Subject criteria*: Subjects will be men and women without existing skin conditions between the age of 18 and 65.

1. *Inclusion criteria*: All subjects should be English-speaking adults between the ages of 18-65. Because this is a not for benefit study and the documents will not be translated, the study will be restricted to English-speakers. This will not affect the scientific validity of the study because language is not a characteristic expected to relate to the health of skin on hands.
2. *Exclusion criteria*: Exclusion criteria will be assessed at enrollment using the baseline survey, a hand exam, and patch testing for all substances included in the study. Subjects indicating a history of dermatitis, who are currently pregnant or trying to become pregnant, who patch test for any substance in the trial, who display baseline skin abnormalities (e.g. open sores or dermatitis) during a hand exam, or who are employed in a profession in which hands are regularly exposed to irritants (for example healthcare workers, mechanics, hairdressers/cosmetologists, bartenders or dishwashers) will be excluded from the sample.
3. *Withdrawal/Termination criteria*: Subjects are free to withdraw from the study at any time without penalty. Any subject presenting with moderate to severe dermatitis (assessed score > 270 on the HECSI scale or as diagnosed by [name]) will be removed from the study unless [name] determines that the reaction observed is not clinically significant. All subjects will receive prompt medical attention if necessary and will subsequently be cleared for continuing participation by [name] or removed from the study. Subjects must participate in 95% of study activities (daily questionnaire and hand exam, daily pickup of new materials, 10x handwashing daily) in order to continue in the study.
4. Subjects may not participate in other studies while participating in this study

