Data collection forms will be reviewed on a daily basis for completeness and to quickly identify major errors. [name] will review HECSI scores and photos of hands to identify any subjects that may be in need of follow up. Compliance with the study intervention will be measured by self-report in the daily questionnaire and by observation of the amount of handwashing substance left by each subject on a daily basis.

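### The 95% participation rule ends observation of randomised subjects on behaviour that the outcome can influence, and the margin of three losses per arm rests on no stated attrition rate

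*Protocol*

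**What the plan says.** Under Subject Characteristics, the Withdrawal/Termination criteria read: "Subjects must participate in 95% of study activities (daily questionnaire and hand exam, daily pickup of new materials, 10x handwashing daily"), and this level is required "in order to continue in the study". No measuring period is given, and the text does not say whether the share applies to each activity or to all of them together. It also does not say what happens to data already collected from a removed subject.

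Under Subject Participation, the Outcome item uses almost the same threshold differently: "We define high compliance as >95% completion of study intervention activities, as measured by survey completion, pickup of materials, and self reported handwashing" ten times a day. There it only describes high compliance. Removal is not mentioned, the hand exam is not listed, and the sign is strictly greater than 95%. The sentence before it says that compliance is measured by self-report and by observing materials. The Data Collection paragraph agrees, adding measurement "by observation of the amount of handwashing substance left by each subject on a daily basis".

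On size, the protocol says: "We plan to enroll 108 total subjects in the study, with 18 randomized to each arm", "with the understanding that minor attrition may occur", and "estimate that we need 15 subjects per arm to complete the study to achieve our goals". Randomisation follows the reading of the baseline patch tests and precedes the four weeks of washing. The Data Analysis paragraph compares the proportion with dermatitis between arms without naming the denominator. The sample size section reads 20-100% in an arm as a problem and 0% as good evidence of potential.

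**The concern.** A rule that removes randomised subjects for what they do after randomisation can undo the comparability that randomisation gave. Here the link to the outcome is close. The outcome is skin irritation from the assigned substance, and using that substance is one of the activities that must reach 95%. Subjects also know whether they have soap, sanitizer or chlorine. Someone with sore hands has an obvious reason to skip washes.

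Removal also ends the daily exam, photographs and questionnaire. Dermatitis that would have appeared later is then never recorded, and no analysis plan can restore it.

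The worst error for this study would be a falsely reassuring arm, because 0% is to be read as a reason to take a method forward. With 15 to 18 subjects per arm, two or three subjects decide that reading. The rule also adds losses that the sample size section does not visibly allow for.

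**Working it through.** **1. The plan's own figures.** 6 arms × 18 = 108, as stated. Going from 18 to 15 allows 3 losses per arm, 3/18 = 16.7%. Conversely 15/(1 − 1/6) = 18. The numbers agree, but the 16.7% is implied by them and stated nowhere. There is no power calculation to reproduce.

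**2. What the margin tolerates.** Let d be the chance that a subject is lost for any reason (assumed, independent between subjects). One arm keeps at least 15 with probability P(Bin(18, 1 − d) ≥ 15); for all six arms, raise this to the sixth power.

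| d | one arm | all six |
|---|---|---|
| 5% | 0.989 | 0.937 |
| 10% | 0.902 | 0.538 |
| 15% | 0.720 | 0.140 |
| 16.7% | 0.648 | 0.074 |
| 20% | 0.501 | 0.016 |

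**3. How strict the rule is.** Four weeks at seven days a week is 28 evenings.
- *Applied to each activity:* 0.95 × 28 = 26.6. So 27/28 = 96.4% passes and 26/28 = 92.9% fails; one evening may be missed. For washes, 0.95 × 280 = 266, so 14 may be missed.
- *Pooled over three daily activities:* 3 × 28 = 84 items and 0.95 × 84 = 79.8, so 80 are needed. A missed evening costs two items (questionnaire with exam, and pickup) if washing continues. Two missed evenings then leave 80/84 = 95.2%, a pass. If a missed pickup also costs a day's washing, two missed evenings leave 78/84 = 92.9%, a fail.
- *Applied as a running share:* one miss before day 20 already falls below 95% (18/19 = 94.7%).

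**4. Attrition under the first two readings.** Let q be the chance of missing any one evening (assumed, independent). The share kept is P(Bin(28, q) ≤ 1) or P(Bin(28, q) ≤ 2), and it replaces 1 − d in step 2.

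| q | misses allowed | share kept | expected of 18 | one arm ≥ 15 | all six ≥ 15 |
|---|---|---|---|---|---|
| 2% | 1 | 0.893 | 16.1 | 0.880 | 0.464 |
| 2% | 2 | 0.982 | 17.7 | 1.000 | 0.998 |
| 3% | 1 | 0.795 | 14.3 | 0.481 | 0.012 |
| 3% | 2 | 0.949 | 17.1 | 0.989 | 0.934 |
| 5% | 1 | 0.588 | 10.6 | 0.026 | 0.000 |
| 5% | 2 | 0.837 | 15.1 | 0.666 | 0.087 |

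**5. Effect on the arm's reading, if removed subjects leave both numerator and denominator.**
- Three cases removed: 4/18 = 22.2% becomes 1/15 = 6.7%, crossing below 20%. 3/18 = 16.7% becomes 0/15 = 0%, which would be read as good evidence.
- Three non-cases removed: 3/18 = 16.7% becomes 3/15 = 20%, reaching the line from below.

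**The case against.** The strongest reply is that bias follows only if removed subjects' data are discarded, and the protocol nowhere says so. The analysis set is commonly left to an SAP, which is not shown. HECSI and self-perception are recorded daily, so a subject sore enough to skip washes would often already have scores on file. This stands for dermatitis seen before removal. It does not answer the loss of observation afterwards, which is a conduct rule set in the protocol.

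Second, the mechanism is an inference. The only burden of daily pickup that the protocol names is the time it takes, which has nothing to do with skin, and step 5 shows that losing non-cases pushes the rate up. A reader might infer that the rule does drop people with painful hands and pulls the arms together. The protocol does not establish that.

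Third, a reader might infer that 18 per arm cannot absorb the rule. It can absorb three losses, and at 5% total loss all six arms keep 15 with probability 0.937. The alarming figures need both the stricter reading and an assumed miss rate.

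Fourth, a reader might infer that compliance rests on self-report alone, or that payment depends on the reported number of washes. Neither is supported: leftover materials are also observed, and payment is per week of intervention completed, with no link to wash counts.

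Last, the study is preliminary and descriptive, and tolerability under near-full exposure is a fair question. That argues for keeping a per-protocol set, not for ending observation.

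**Conclusion.** The point holds in a limited form. As written, the protocol ends follow-up of randomised subjects on a criterion that irritation can influence, and what happens after removal cannot be recovered later. Three removed cases are enough to move an arm from 22% to 7%, or from 17% to 0%. That size assumes that the removed subjects are cases and are left out of the analysis; the first is likely but undocumented, the second is unstated.

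The margin of three per arm is thin and unsupported by any stated rate, but not shown to be inadequate. At 2% and 3% missed evenings, the chance that all six arms keep 15 runs from 0.46 and 0.01 to 0.998 and 0.93, depending on which reading of the 95% is meant. These figures assume 28 evenings, independent misses and no other losses. That spread is itself a reason to fix the definition, and the two uses of 95% in the protocol need to be reconciled.

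**What to change.** - Do not use the 95% threshold to end observation. Continue the daily exam and questionnaire to Day 28 for every willing randomised subject, whatever the adherence. Observation can continue without continued washing, and the separate dermatitis-based removal rule is not affected.
- Analyse all randomised subjects in their assigned arm, and count dermatitis recorded before any exit as a case.
- Use 95% only to define a secondary per-protocol set. Give it one definition in both places: which activities count, pooled or separate, over what period, and at least or more than 95%. Base it on the leftover volume already observed daily alongside self-report.
- State the attrition rate behind 18 enrolled for 15 completers.

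The cost is a protocol amendment and some analysis wording. The small downside is some diluted exposure in the main analysis, which the per-protocol set covers.
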